#### Secondary objectives

Assess the impact of a precision medicine platform on the individual components of the composite outcomes of patients with diabetes.Evaluate the impact of a precision medicine platform on hospitalisation rate secondary to heart failure.Evaluate patients’ adherence to antidiabetic medications, cholesterol-lowering medications and antihypertensives.Evaluate the impact of iDiabetes platform treatment recommendations on the rate of severe hypoglycaemia.Evaluate whether recommendations from iDiabetes platform improve healthcare professionals’ compliance with guideline recommendations during the prescription of antidiabetic medications.

Additional exploratory objectives will include further assessment of the impact of iDiabetes on end-organ diabetes-associated complications, qualitative and cost-effectiveness analysis of the platform. A full list of exploratory objectives can be viewed in the online supplemental file 1.

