#### iDiabetes (guideline support)

Patients will attend their annual diabetes review and be assessed as per usual care including routine diabetes blood testing (see table 1). The iDiabetes platform will generate automated, individualised treatment recommendations using routine clinical data and blood test results from annual appointments. Recommendations will be determined by the latest treatment guidelines such as the *American Diabetes Associations’ Standard of Care for Diabetes* and the *National Institute for Health and Care Excellence Clinical Knowledge Summaries*.^15 16^ Recommendations on optimisation of medications for associated comorbidities will also be provided where a patient has renal or cardiovascular disease. For example, advice will be given to optimise ACE inhibitor or angiotensin receptor blocker for patients with proteinuria or optimise statins for patients with cardiovascular disease.

**Table 1 T1:** Blood tests, risk scoring systems and imaging tests performed by iDiabetes platform.

	Blood tests	Risk scoring	Imaging
Renal	▪ Creatinine▪ Laboratory-measured eGFR▪ Urinary albumin:creatinine ratio**▪ eGFR calculated by 2021 CKD-EPI Creatinine**	**▪ Kidney failure risk equation**	
Cardiology	▪ **NT-proBNP▪ hsTroponin I**	▪ **Coronary Artery Disease Polygenic Risk Score**	▪ **Echocardiography (either standard echocardiography or AI decision-supported [US2Ai] echocardiography)***
Liver	▪ ALT▪ Bilirubin▪ Alkaline phosphatase▪ **AST**▪ **Ferritin/ transferrin saturations**†▪ **Hepatitis B and C**†	▪ **FIB-4 score**†▪ **NAFLD Fibrosis Score (NFS)**†▪ **Enhanced Liver Fibrosis (ELF) Score**†	▪ **Liver Fibroscan**†
Diabetes aetiology	▪ HbA1C▪ **C-peptide and paired glucose**‡▪ **Pancreatic autoantibodies testing**‡	▪ **Type 1 Diabetes Polygenic Risk Score**‡▪ **MODY probability**‡	

Tests in bold will be performed in *iDiabetesPlus* arm only

* US2.AI-supported echocardiography will be performed in patients with NT-proBNP between 400 and 2000 pg/mL pg/mL. Standard echocardiography will be performed via the current urgent clinical pathway if NT-proBNP >2000 pg/mL.

† Non-invasive lliver ffibrosis sscoring, ferritin/ transferrin saturations and hepatitis B and C testing if ALT >30 IU/L. ELFELF testing will be triggered if FIB-4 >1.45 or NFS >−1.455. Fibroscan will be performed on patients with FIB-4 >3.25, NFS >0.677 or ELF ≥9.8.

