#### Usual diabetes care

This will form a control arm. Patients will attend their usual annual diabetes appointment and be managed as per the usual care by their diabetes care provider, with no additional intervention from the iDiabetes platform or study team.

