#### Secondary outcomes

All-cause mortality rate.All-cause hospitalisation rate.Proportion with >40% eGFR reduction from baseline, or new end stage kidney disease.Proportion with absolute HbA1C reduction >0.5% (>5.5 mmol/mol).Hospitalisation rate secondary to heart failure.Drug adherence (medication possession ratio).Rate of severe hypoglycaemia.Proportion of patients treated according to guidelines.

Outcomes which can be measured in the *usual diabetes care* arm as well as the iDiabetes intervention arms have been selected to allow comparison. Therefore, in decreasing order of importance, we rank (1) all-cause mortality, as failure to consider mortality can introduce issues of competing risk; (2) all-cause hospitalisations, as these are common and a major burden to patients and healthcare systems; (3) renal function decline, as this is a major morbidity in diabetes—a fall in eGFR of >40% is in keeping with clinical trials focusing on renal outcomes as the endpoint; (4) HbA1c reduction >0.5% (5.5mmol/mol), as HbA1c is a major driver of both microvascular and macrovascular disease in diabetes. HbA1c is not ranked higher despite its importance in diabetes as many treatment recommendations provided by iDiabetes (eg, for heart failure, coronary artery disease, renal disease and steatotic liver disease) are HbA1c independent, in which HbA1c lowering is not our primary goal. All items in the composite will also be analysed and reported individually as secondary outcomes. All outcomes will be measured at individual patient level.

Additional exploratory outcomes will include further assessment of the impact of iDiabetes on end-organ diabetes-associated morbidity and diabetes treatment and a full qualitative and cost-effectiveness analysis of the platform. A full list of exploratory outcomes can be viewed in the online supplemental file 1.

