### Quantitative data collection and management

Blood and urine specimens will be taken from all patients during annual diabetes review appointments as part of routine clinical care. Additional testing will be performed on specimens from *iDiabetesPlus* clusters through a reflexive laboratory cascade system if criteria are met (see table 1). Data will be collected for study outcome evaluation through routine data linkage, with clinical records and prescription encashment records used to evaluate medication adherence. All data will be analysed within a digital Trusted Research Environment (TRE) within the NHS Tayside and Fife Health Informatics Centre. All patient-identifiable information will be anonymised within the TRE to ensure patient confidentiality. Data from patients in the study will be linked to their electronic medical records for long-term follow-up for up to 15 years.

The data management plan for the study was developed according to the Tayside Medical Science Centre standard operating procedure for data management.^19^ As the iDiabetes platform is designed to integrate with routine diabetes clinical care, no efforts will be made to promote patient retention or completion of follow-up annual review appointments who would not ordinarily attend, to reflect real life circumstances.

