#### Secondary statistical analysis

The main secondary analyses will consist of the comparisons between arms for individual components of the composite, that is, all-cause mortality, all-cause hospitalisation rate, proportion with >40% eGFR reduction from baseline, new development of ESRD and proportion with absolute HbA1C reduction >0.5% (>5.5 mmol/mol). Secondary outcomes as listed in the study outcomes above will also be analysed, treating these as exploratory analyses.

All analyses will be on an intention-to-treat basis.

A full statistical analysis plan will be published prior to data-lock.

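### The between-arm comparison of the medication possession ratio is conditioned on being supplied the drug, which the platform is meant to change, so it is not an intention-to-treat contrast and can be biased in either direction

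*Protocol article*

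**What the plan says.** Adherence is a stated secondary objective: "Evaluate patients’ adherence to antidiabetic medications, cholesterol-lowering medications and antihypertensives". The Secondary outcomes list names the measure as "Drug adherence (medication possession ratio"), and the section on quantitative data collection gives the source: "with clinical records and prescription encashment records used to evaluate medication adherence".

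The intervention works on prescribing of the same drug groups. In the guideline-support arm, besides individualised treatment recommendations, "advice will be given to optimise ACE inhibitor or angiotensin receptor blocker for patients with proteinuria or optimise statins for patients with cardiovascular disease". The iDiabetesPlus section adds an algorithm for selecting treatment. Usual care proceeds "with no additional intervention from the iDiabetes platform or study team". Change in prescribing is itself a secondary outcome: "Proportion of patients treated according to guidelines".

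The Secondary outcomes section says that the outcomes were picked so that the intervention arms can be compared with usual care. The Secondary statistical analysis section says "All analyses will be on an intention-to-treat basis". It treats the listed secondary outcomes beyond the composite's components as exploratory and promises a full analysis plan before data-lock. The article does not say which patients enter the possession ratio.

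**The concern.** A possession ratio is supply held divided by time on the drug. A patient never supplied a drug group has no ratio for it, so on the ordinary reading of the measure the comparison covers people supplied the drug during follow-up. Supply during follow-up comes after randomisation and is what the recommendations aim to alter. If the platform works as intended, the iDiabetes arms will contribute a different mix of established users and new starters from usual care.

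The two groups are then no longer comparable by virtue of randomisation, and a difference in mean ratio mixes two things: how patients behave, and who was started on treatment. The platform could appear to harm or to improve adherence although no established user and no new starter behaves differently in either arm.

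**Working it through.** The article gives no possession ratio, standard deviation, rate of drug use or power for adherence, so there is no stated figure to reproduce. The check asks what happens to the mean ratio when behaviour is the same in both arms and only the share of new starters differs.

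**Inputs from the article.** 7500 patients per arm. Up to 60 clusters allocated 1:1:1, hence 20 per arm. ICC 0.05 (composite simulation) and 0.03 (hospitalisation power). Neither ICC was given for adherence.

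**Assumed inputs.** Share already on the drug group, b = 50%. New starts, s = 5% in usual care and 15% in an iDiabetes arm. Mean ratio in established users, Mp = 0.85. Mean ratio in new starters, Mn = 0.65. Mp and Mn are the same in both arms. SD 0.25. ICC 0.01 is added as a low value.

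**Mean ratio among those supplied** = (b × Mp + s × Mn) / (b + s)

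- Usual care: (0.425 + 0.0325) / 0.55 = 0.832
- iDiabetes: (0.425 + 0.0975) / 0.65 = 0.804
- Apparent difference: -2.8 points; true behavioural difference: zero

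**Standard error.** Patients with a ratio: 7500 × 0.55 = 4125 and 7500 × 0.65 = 4875, or 206.25 and 243.75 per cluster. Design effect = 1 + (patients per cluster - 1) × ICC. SE = 0.25 × √(DE₁/4125 + DE₂/4875).

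| ICC | DE usual care | DE iDiabetes | SE | z |
|---|---|---|---|---|
| 0.01 | 3.05 | 3.43 | 0.0095 | about -2.9 |
| 0.03 | 7.16 | 8.28 | 0.0147 | about -1.9 |
| 0.05 | 11.26 | 13.14 | 0.0184 | about -1.5 |

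**Sensitivity.** b varied over 30%, 50% and 70%; new starts 5% in usual care v 10%, 15% or 20% in iDiabetes:

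| Mp | Mn | Apparent difference (points) |
|---|---|---|
| 0.85 | 0.65 | -1.2 to -5.1 |
| 0.85 | 0.75 | -0.6 to -2.6 |
| 0.85 | 0.85 | 0 |
| 0.80 | 0.85 | +0.3 to +1.3 |

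Some cases pass 1.96 even at the higher ICCs. With b = 30%, Mn = 0.65 and 5% v 15%, the difference is -3.8 points and z is -2.5 at ICC 0.03 and -2.0 at ICC 0.05. Many do not.

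**The same base case in populations that do not depend on arm.** Established users only: 0.85 v 0.85, difference zero. Coverage over all enrolled, non-users counted as zero (b × Mp + s × Mn, treating new starters as if on the drug throughout follow-up): 0.458 v 0.522. The first shows unchanged behaviour and the second shows greater uptake, and both are right.

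**The case against.** The strongest reply is that the article names a measure and nothing more. Population, index date and handling of switches belong in the analysis plan, which is promised and not shown. A possession ratio in a well-chosen population is acceptable, and the fix below still uses one. This stands in part: nobody can say that the trial team has chosen the wrong population. But the named measure in its usual form gives the arm-dependent comparison unless someone specifies otherwise, and the article promises intention to treat for every analysis without reconciling the two.

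Second, clinical records are used as well as encashment records, so a patient prescribed a drug but never supplied it could be scored zero. That widens the set but does not free it from arm, because being prescribed also follows from the recommendations.

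Third, every input that determines the size is assumed, the platform only recommends, and the statin and ACE inhibitor or ARB examples concern patients with particular comorbidities. A ten-point excess of new starts among all enrolled may be too high. This stands.

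A reader might infer that iDiabetes will show worse adherence, or that the artefact will be statistically significant. The article supports neither. The direction requires new starters to have lower ratios than established users, and the base case passes 1.96 only at an ICC below both values that the protocol uses. A reader might also infer that the economic evaluation would be misled, since that section calls adherence to the treatment plan essential. That section gauges uptake and adherence through the discrete choice experiment, not through the possession ratio.

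**Conclusion.** The concern holds as a matter of design. Read in its usual way, the named measure conditions on an event after randomisation that the intervention targets, which does not fit the intention-to-treat statement or the aim of comparability between arms. That conclusion needs only that the recommendations change who is supplied the drugs.

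The magnitude is illustrative. Under the stated assumptions the spurious difference is -2.8 points in the base case; across the scenarios tried it runs from -5.1 to +1.3 points, and it is nil where new starters and established users have the same ratio. The outcome is secondary and exploratory and the primary result is untouched, so this is worth settling before the data are seen but does not threaten the trial.

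**What to change.** Define the adherence outcome in three parts, using the same records:

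1. **Adherence, compared between arms.** The possession ratio among patients already dispensed a drug in the group within a fixed window before enrolment, for each of the three groups in the secondary objective (antidiabetic, cholesterol-lowering, antihypertensive). Working at group level means that a switch within a group is not scored as non-adherence. End the denominator at a recorded prescriber stop.
2. **Uptake, compared between arms.** The proportion of follow-up days covered by the drug group in all enrolled patients, non-users counted as zero. This is the intention-to-treat measure; label it uptake, not adherence.
3. **New starters.** Report their ratio descriptively, by arm, without a test.

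The group level and the stop rule matter. If the ratio were kept by individual drug class over the whole of follow-up, and an assumed extra 10% of baseline users in the iDiabetes arm were switched out of the class halfway through, the false loss would be 0.10 × 0.85 × 0.5 = 4.3 points, larger than the base-case artefact.

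The cost is a few lines of definition and a little extra analysis. The first measure says nothing about new starters, including newly diagnosed patients with no earlier antidiabetic supply, which is why the other two are reported beside it. It also depends on stops being recorded equally well in all arms.

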## Data collection, management and analysis

### Study assessments

There will be no research-specific study visits for primary and secondary outcomes as data will be collected from routine assessments during annual diabetes review, and patient consent will be undertaken at a cluster level (see *iDiabetes Study Consent* below).

### Quantitative data collection and management

Blood and urine specimens will be taken from all patients during annual diabetes review appointments as part of routine clinical care. Additional testing will be performed on specimens from *iDiabetesPlus* clusters through a reflexive laboratory cascade system if criteria are met (see table 1). Data will be collected for study outcome evaluation through routine data linkage, with clinical records and prescription encashment records used to evaluate medication adherence. All data will be analysed within a digital Trusted Research Environment (TRE) within the NHS Tayside and Fife Health Informatics Centre. All patient-identifiable information will be anonymised within the TRE to ensure patient confidentiality. Data from patients in the study will be linked to their electronic medical records for long-term follow-up for up to 15 years.

The data management plan for the study was developed according to the Tayside Medical Science Centre standard operating procedure for data management.^19^ As the iDiabetes platform is designed to integrate with routine diabetes clinical care, no efforts will be made to promote patient retention or completion of follow-up annual review appointments who would not ordinarily attend, to reflect real life circumstances.

### Qualitative data collection and management

This nested qualitative study will explore the views and experiences of those delivering and receiving *iDiabetes* and *iDiabetesPlus* care, using semistructured interviews with patients and health professionals involved in the implementation and use of the iDiabetes platform and the delivery of iDiabetes-informed care.

Semistructured interviews will be conducted with patients and clinical and non-clinical primary care staff from clusters allocated to the iDiabetes platform and will be carried out in three rounds. An initial round of interviews will be carried out to coincide with the phased implementation of iDiabetes, the second round of interviews will target participants after their first annual review following iDiabetes implementation and the third round of interviews target participants after their second annual review under iDiabetes care. For patients’ interviews, the focus will be on their experiences of iDiabetes and its impact on them and their diabetes care. The interviews with staff will explore their views and experiences of implementing and using iDiabetes in their clinical practice. Qualitative data collected will form part of a process evaluation of the iDiabetes intervention, and insights gained will help inform future refinements to the platform.

Audio-recorded data from the interviews will be transcribed verbatim. Any relevant documentary data (eg, guidance, policies and training materials) will be included in the qualitative dataset. All qualitative data will be stored in encrypted folders on secure University of Dundee servers.

### Health Economics data collection and management

Alongside clinical effectiveness, the iDiabetes platform must also represent value for money to the healthcare system. To assess this, a cost-effectiveness health economic evaluation will be conducted using the quantitative study data.

If implemented, the iDiabetes platform will affect treatment plans for patients. For any predicted improvement in health outcomes to be achieved, patient adherence to the treatment plan is essential. To gauge uptake of and adherence to the iDiabetes platform, patient preferences will be explored using the discrete choice experiment (DCE) methodology. DCEs have been widely used in health economics to assess patient and public preferences, including preferences for personalised diabetic management.^20^ In the developmental stages of the DCE, ‘think aloud’ interviews will be held with a subsample of the study population to test and refine the survey. DCE data collection will involve inviting participants to complete an online survey.

No personally identifiable information will be collected in the DCE survey. Data generated by the DCE will be stored on secure University of Aberdeen servers, in password-protected folders which are only accessible to the research team.

### Data analysis

#### Primary statistical analysis

The primary composite endpoint will be analysed using the Win-Ratio (WR) method. This approach is hierarchical, allowing for sequential analysis of prespecified endpoints within the composite in the order of clinical importance. The WR allows for a combination of quantitative outcomes, such as HbA1C and eGFR reduction, with time-to-first occurrence outcomes such as time to death or hospital admission, in contrast to other conventional statistical methods that only allow time-to-first occurrence of any event in the composite.^21^

In this study, the most clinically important endpoint, all-cause mortality, will first be compared between a patient in one study arm to a patient in the comparator arm. If a patient reaches this endpoint first the result will be considered a ‘loss for that patient’s arm’ and a ‘win’ for the comparator arm and no further endpoints are assessed for that pairing. If neither patient ‘wins’ for this outcome, then the next highest priority endpoint will be compared, until all endpoints have been compared sequentially (see *Primary outcome* for endpoint hierarchy). If neither patient in a pairing ‘wins’ according to any of the endpoints, then that pairing is considered a ‘draw’. The statistical analysis will compare every patient in one arm with every patient in the comparator arm. For example, if comparing *iDiabetes (guideline support*) to *iDiabetesPlus,* then all 7500 patients in one arm will be compared with all 7500 patients in the comparator arm, for a total of 56 250 000 opportunities for ‘wins’, ‘losses’ or ‘draws’. The total number of ‘wins’ for each arm will be calculated. An arm will be considered superior to the comparator if there are statistically significant increased number of ‘wins’ in that arm compared with the comparator arm. The WR will be estimated and statistical significance will be considered for the primary outcome at the 5% level.

For the statistical analysis, in a Hochberg hierarchical procedure, the primary comparison will first be made between the *iDiabetesPlus* and *usual diabetes care* arms. If there is a significant ‘win’ in the *iDiabetesPlus* arm compared with *usual diabetes care* for the composite primary study outcome, a comparison will then be made between the *iDiabetes* (guideline support) and *usual diabetes care* arms. If the iDiabetes (guideline support arm) is also demonstrated to be superior to the *usual diabetes care* arm, then a final comparison between the *iDiabetesPlus* and *iDiabetes* (guideline support) arms will be undertaken. This will inform whether enhanced phenotyping and genotyping provide additional advantages over conventional treatment recommendations based on guidelines.

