## Methods

### Study design

This is a three-arm cluster-randomised controlled study (two iDiabetes arms and usual diabetes care control arm), with a nested qualitative study and economic evaluation. The inclusion of two different arms within the iDiabetes platform allows evaluation of the clinical utility and cost-effectiveness of the addition of guideline-based recommendations (*iDiabetes (guideline support*)) to patients’ usual diabetes care as well as the additional value gained from precision diagnosis and treatment resulting from the addition of enhanced phenotyping and genotyping to guideline support (*iDiabetesPlus arm*).

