### Randomisation

Each primary care general practice (GP) within the National Health Service (NHS) Tayside Scottish Health Board region will form one of up to 60 clusters. NHS Tayside provides primary healthcare to approximately 417 650 people in the northeast of Scotland, in both urban and rural communities within the region.^12^ Practices will be stratified by population size (<6000 or ≥6000 registered patients) and index of deprivation deciles (1–3 high deprivation, 4–7 medium and 8–10 low).^13^ Clusters will be randomised to one of the following three arms: *iDiabetes (guideline support*), *iDiabetesPlus* or *usual diabetes care* (see figure 1). All 60 clusters (approximately 400 patients per cluster) will undergo initial randomisation to the iDiabetes platform or *usual diabetes care* arms in a 2:1 ratio. Clusters initially allocated to the iDiabetes platform will undergo a second randomisation to *iDiabetes (guideline support*) or *iDiabetesPlus* in a 1:1 ratio, resulting in overall cluster allocation of 1:1:1 for *iDiabetes (guideline support*), *iDiabetesPlus* and *usual diabetes care* arms.

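### The added-value test (iDiabetesPlus v guideline support) on the primary composite is gated behind guideline support beating usual care; the gate blocks it when guideline support has little or no effect and is not needed for error control

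*Protocol article*

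**What the plan says.** Under Primary statistical analysis, the protocol article sets the order of the three pairwise win-ratio comparisons: "For the statistical analysis, in a Hochberg hierarchical procedure, the primary comparison will first be made between the" Plus and usual care arms. If Plus wins "for the composite primary study outcome, a comparison will then be made between the" guideline support and usual care arms. The last step, Plus v guideline support, carries a second condition: "If the iDiabetes (guideline support arm) is also demonstrated to be superior to the" usual care arm. No other route to that comparison on the composite is described, and no reason is given for the second condition.

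The section gives the purpose of the last step: "This will inform whether enhanced phenotyping and genotyping provide additional advantages over conventional treatment recommendations based on guidelines". Study design gives the same purpose as one of two reasons for having two platform arms: to evaluate guideline support added to usual care "as well as the additional value gained from precision diagnosis and treatment resulting from the addition of enhanced phenotyping and genotyping to guideline support".

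On error rates, "statistical significance will be considered for the primary outcome at the 5% level"; whether this is one-sided or two-sided is not stated. Under Randomisation, clusters are divided equally, "resulting in overall cluster allocation of 1:1:1 for" the three arms.

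**The concern.** The condition makes one question wait on the answer to another. Suppose the benefit comes wholly from the extra testing and guideline recommendations alone change little. That is when the contrast between Plus and guideline support is largest, yet guideline support will then usually fail to beat usual care and the sequence stops before the contrast is tested.

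The trial could then report that Plus beats usual care and that guideline support was not shown to. It would have no confirmatory statement on the composite that Plus beats guideline support. One significant and one non-significant result against a common control do not establish a difference between the two platform arms.

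**Working it through.** **1. The plan's own pairwise power figure.** Power for individual outcomes states 81% for hospitalisation, 45% v 37%, with 40 clusters, ICC 0.03 and alpha 0.05. Take 20 clusters per arm and 375 patients per cluster (7500 per arm).
- Design effect = 1 + 374 × 0.03 = 12.22.
- Effective n per arm = 7500 / 12.22 = 613.7.
- SE under the null = √(2 × 0.41 × 0.59 / 613.7) = 0.0281. SE under the alternative = √((0.45 × 0.55 + 0.37 × 0.63) / 613.7) = 0.0280.
- Power = Φ((0.08 − 1.96 × 0.0281) / 0.0280) = 81.4%.

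With 400 per cluster it is 81.6%. The stated 81% is reproduced.

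**2. Power for the composite, pairwise: an assumption.** The article gives 413/500 = 82.6% at a win ratio of 1.20 with 60 clusters of 40 patients. A pairwise comparison has about 40 clusters. If all 60 clusters were shared between two simulated arms:
- SE(log WR) = ln 1.20 / (1.960 + 0.938) = 0.0629.
- For 40 clusters, 0.0629 × √(60/40) = 0.0770.
- Power = Φ(0.1823 / 0.0770 − 1.960) = 66%.

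The real clusters are about ten times larger, so true power could be higher. The range used for Plus v usual care is 67% to 99%.

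**3. The gate in terms of z.** With three arms of equal precision, z(Plus v guideline) = z(Plus v usual) − z(guideline v usual). Winning all three steps at 1.96 therefore needs z(Plus v usual) of at least 1.96 + 1.96 = 3.92.

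**4. Chance of a confirmed Plus v guideline support claim.** Three independent normal arm estimates with equal variance, two-sided 5% tests, 2 million draws. Each cell is with the gate v without it.

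| Power, Plus v usual care | Guideline effect nil | Guideline effect half of Plus |
|---|---|---|
| 67% | 0.5% v 52% | 1.2% v 20% |
| 82.6% | 1.0% v 72% | 3.5% v 29% |
| 90% | 1.4% v 83% | 6% v 36% |
| 99% | 2.3% v 98% | 25% v 57% |

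In the nil column, the last test is reached in 2.4% to 2.5% of trials, or 2.5% to 3.6% of those in which Plus beats usual care. The gate opens only through the 2.5% upper-tail error of guideline support v usual care, so a larger trial does not help. With a quarter of the Plus effect and 82.6% power, the last test is reached in 10.6% of trials and the claim is made in 2.6% v 54%.

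**5. Does the gate protect the error rate?** If guideline support = usual care and Plus = guideline support, then Plus = usual care. So every intersection of the three nulls contains, or implies, the null for Plus v usual care. By the closure principle, once that null is rejected at 5%, each of the other two can be tested at the full 5%. Simulated family-wise error without the middle gate:
- all arms equal: 4.97%
- only Plus works: 3.5% (noncentrality 2.9) and 5.02% (noncentrality 10)
- Plus = guideline support, both better than usual care: 3.5% and 4.99%
- Plus = usual care, guideline support different: 4.97%

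The Monte Carlo standard error is √(0.05 × 0.95 / 2,000,000), about 0.015 percentage points, so nothing exceeds 5% beyond simulation error. The largest value with the gate is the same.

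**6. The label.** Hochberg's procedure is a step-up test on ordered p-values and has no such gate. Applied to all three tests, it would give about 73% for Plus v guideline support when only Plus works and Plus v usual care has 82.6% pairwise power, against 1.0% for the described sequence. The name and the steps therefore give very different answers.

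**The case against.** The fixed sequence is a valid procedure and controls family-wise error. It also has a coherent reading: show that the full platform works, show that the simpler one works, then ask whether the extra testing adds to a working base. Plus v usual care, which the article calls the primary comparison, is untouched by the gate, and added value is only one of the two reasons given for having two platform arms. All of this stands. The fault is an unneeded condition that defeats a stated purpose, not a broken error rate.

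A reader might infer that the added-value claim is almost unreachable. The documents do not support that in general. Figures near 1% belong to a guideline effect of nil, or to modest power. With half the Plus effect the gated chance is 25% at 99% power and about 70% (v 85% ungated) at a noncentrality of 6 for Plus v usual care.

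A reader might also infer that Plus and guideline support would never be compared. Secondary statistical analysis plans between-arm comparisons of each component, with no gate stated. What is blocked is the test on the primary composite.

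The technical objection is the strongest. The article defines superiority by a significant excess of wins, so its natural null is win ratio = 1, and win-ratio relations need not be transitive. In theory guideline support could tie with both other arms while Plus beats usual care, and step 5 would then fail. The normal-means simulation imposes transitivity and cannot settle this; one intransitive example simulated separately stayed at about 5% to 6%. The full-5% argument therefore depends on how the null is stated. The gate is still not needed: Holm or Hochberg on the two remaining tests would keep control without it.

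**Conclusion.** The point holds for the confirmatory test on the primary composite, and most strongly when guideline support has little or no effect. With no effect, the test is blocked about 97% of the time at any trial size. With part of the Plus effect, the gate costs power by an amount that depends on the effects and shrinks as they grow.

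The block under a nil effect does not depend on the assumed power. The claim probabilities do: they rest on 67% to 99% power for Plus v usual care, equal precision in the three arms, approximately normal test statistics and two-sided 5% tests. The finding that both remaining comparisons can be tested at the full 5% rests on nulls of equal outcome distributions. The mismatch between the Hochberg label and the described steps stands on the text alone.

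**What to change.** Rewrite the testing paragraph in the protocol and carry it into the SAP, which the article says will be published before data-lock:

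- Test Plus v usual care first, at two-sided 5%, as the single gatekeeper.
- If it is significant, test guideline support v usual care and Plus v guideline support in parallel, each at two-sided 5%, with the nulls stated as equality of outcome distributions.
- If the null is to be win ratio = 1, apply Holm or Hochberg to those two tests instead.
- Replace the description as a Hochberg hierarchical procedure with a name that fits the steps.

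With nulls of equal distributions, this costs wording only: the first two tests keep their present order and level, and the third gains power. The Holm or Hochberg version can cost guideline support v usual care some power, because that test may then be held to 2.5%. Neither version needs more patients or data.
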